### Data collection methods

Full description of the study instruments and timeline of administration are given in Table 1. A specifically designed case report form (CRF) will be used to collect the data using paper forms. A defining characteristic of pragmatic trials includes the use of simple easy-to-administer case report forms and psychometric tools. To ensure the feasibility of our baseline assessment instruments, we have elected to include as few psychometric tools as possible. For instance, we are only using a single depression scale and quality of life measure. The BDI-II includes 21 items measured on a scale of 0–3, with higher scores indicating a higher depressive symptom severity [32]. The BDI-II score is analyzed using four categories of depressive symptom severity [32]. We have chosen the BDI-II for two purposes. Firstly, the BDI-II will measure depression severity among participants [33]. The BDI-II identifies prognostically relevant depressive symptoms, such that it strongly predicts a variety of patient-important outcomes for populations suffering with depressive disorders [34]. Patient-important outcomes correspond to meaningful endpoints which identify closely with the patients values and preferences within this population, which may include physical or emotional symptoms, quality of life or social factors such as ability to obtain employments. Secondly, the BDI-II was chosen as a safety measure for the trial which is described later in the data-monitoring section of the trial protocol.

### Qualitative data collection

Using the methodology of Grounded Theory [35, 36], we will engage in an iterative data collection and analysis process to address our two qualitative research objectives.

Research objective (a) will be pursued by collecting focus group data from patient participants in the intervention and control arms and from clinicians involved in those patients’ care.

We have chosen to use focus groups for this objective to enable participants to build off of each other’s ideas and respond to the feedback shared by the other participants. These focus groups ask participants to comment on their shared experiences as a group, and therefore, the focus group is an appropriate method of data collection [37, 38]. Additionally, since the intervention being studied is a group-based program that aims to increase interaction and communication skills of patient participants, a focus group setting will be familiar to the patient groups. We will conduct homogeneous focus groups composed of either 4–7 patients or 4–7 clinicians at 3 time points: during weeks 3, 6, and 18 of the program. All program participants and their clinicians will be invited to participate, and anyone who is willing will be able to participate in a focus group. Focus groups will be conducted by a trained qualitative researcher who is not a clinician involved with patient care. Focus groups will be audio-recorded, and those recordings will be professionally transcribed for analysis [39]. A second researcher will take field notes during the focus group, noting body language, group dynamics and other aspects which are not recorded on the audiotape [37]. We will not be collecting this information (body language) for later use in a discourse analysis. Since we are administering a new intervention, it is important that we record all aspects of face-to-face contact, including during the qualitative sessions. The question guide for the focus groups will evolve throughout the process to reflect the emerging theory but will focus on the participant’s experience of the program and actively solicit constructive feedback to improve the intervention and ensure that it is as acceptable as possible to both patients and clinicians [35, 40]. For example, we might ask patients if the number of visits per week is manageable, if the timing of the program is acceptable, what barriers they experience to attending, what activities they find are particularly helpful or unhelpful etc. The focus group and interview guides are available from authors upon request. We might ask clinicians about their perceived need for this type of program for their patients, their willingness to refer patients to the program and whether they have observed a change in their patient since beginning the program.

Research objective (b) will be accomplished through individual interviews with patients (all patients will be invited to participation in these interviews) from both the control and intervention arms of the randomized study. Each patient will be interviewed twice, during weeks 2 and 10 of the program. Individual interviews were chosen to allow the participant the confidentiality to speak frankly about personal and sensitive issues. Participants will be asked about their perceptions of their depression and how it affects their quality of life, in whatever way they define quality of life. Participants will be asked whether they feel the program is tailored towards their needs and what changes should be made to address such needs. Answers to these questions will allow us to ensure that the program is patient-centred. Congruent with Grounded Theory, we will use purposive and theoretical sampling, and data collection will conclude when theoretical saturation is reached [35]. Theoretical saturation means that additional data collection does not yield new ideas or themes [35]. The individual interviews will be audio-recorded and professionally transcribed [39].

### Data management

Data from CRFs will be entered into research Electronic Data Capture (REDCap) (http://project-redcap.org/). Paper copies of the data will be stored securely as source documents, and electronic data will be hosted in the local institution server with passcode protection and electronic security measures in keeping with institutional policy and privacy regulations. Reports will be generated weekly to check data quality and missingness, whereby we will determine which variables are not being collected or captured properly.

### Statistical analyses

Data generated from the pilot study will help inform the main trial by testing the study procedures. Therefore, no formal statistical analyses will be performed for the pilot data. Description of the study participants and simple tabulation of the pilot data will be presented. Data exploration will be performed to compare the mean difference (and 95 % confidence intervals) of the BDI-II and quality of life scores between intervention and comparator groups at the end of the trial using *t* test and within groups for repeated measures using analysis of variance (ANOVA). All randomized participants will be included in the analyses. The statistical analyses of the pilot data will be exploratory only as the sample size will not allow for definitive analyses. We will use Stata version 12 software for analyses.

Summary of the study objectives and proposed statistical analyses are presented in Table 2. We will consider the following criteria to deem the study is feasible to be conducted:At least 20 % of potential participants agree and enrol in the study (given the time commitment of 18 weeks and frequency of face-to-face visits we would expect fewer participants to enrol)Completion rate of 80 %, that is to say, we will have final visit data on at least 80 % of the participantsWe expect 80 % completion of weekly measurement scales

**Table 2 Tab2:** Summary of the study objectives, outcomes and analysis plans

Aim	Objectives	Outcome	Hypothesis	Statistical analysis
Primary	Assess feasibility of recruitment, retention, group size and data completion	Recruitment and retention rates, data missingness	BA is feasible and acceptable	Descriptive statistics: mean and SD for continuous variables and proportions for dichotomous variables
	Assess resources needed	Group and interview rooms needed, number of clinicians to deliver groups, average length of group session (time needed per session)		Descriptive statistics: mean and SD for continuous variables and proportions for dichotomous variables
	Participants’ feedback and personal experiences	Qualitative study feedback		Qualitative study results based on grounded theory
Secondary	Clinical outcomes: BDI-II and quality of life	Rate of completion of the scales	The intervention group will show improvement in these scales	Between and within group comparisons of the BDI-II and quality of life scales

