**Fig. 2 Fig2:**
[figure not shown]
Pilot study components. a-eligibility and consent, b-baseline interview, diagnosis and demographics, c-physical measurements (height, weight, body fat percent), d-blood draw, e-Beck Depression Inventory (BDI II), f-Behavioural Activation for Depression Scale (BADS), g-Quality of life scales (SF-12, WSAS, and Q-LES-Q-SF), h-Leisure Motivation Scale (LMS), i-assumptions of risks, j-Physical Activity Readiness Questionnaire (PAR-Q), k- Activity tracking form, l- EQ-5D-5L a standardized instrument to measure health outcomes, m-qualitative individual interviews, n-focus group. S1-behavioural activation for depression, S2-values assessment, S3-goal setting, S4-Breaking it down, S5-avoidance and depression, S6- rumination, S7-ruminations II, S8-relationships, S9-involving others and social skills, S10-asseriveness and communication skills, S11-assetiveness and relaxation strategies, S12-leisure education, S13-problem solving, S14-team building and cooperative games, S15-nutrition and laughter yoga, S16- mindfullness and planning of group outing, S17-understanding sleep, S18-group outing, S19-getting back to work and volunteering, S20-S23 and S25-27 relapse prevention and troubleshooting, S24-booster group/adventure based day trip, S28-booster session and end of study. The qualitative components (l and m) are delivered in the pilot phase only. Adapted from Perera et al. [31]

**Table 1 Tab1:** Pilot study instruments

Instrument	Purpose	Administered	Time to complete (min)	When to complete	Intervention	Control
Baseline questionnaire	Baseline data	Clinician/research assistant	60	Baseline	✓	✓
PAR-Q	Assess readiness for physical activity	Self	10	Baseline	✓	
Assumption of risk form	Inform about risks of attending program	Self	5	Baseline	✓	
BDI-II	Monitor depressive symptoms	Self	5	Baseline	✓	✓
				Weekly	✓	✓
				End of study	✓	✓
SF12, WSAS, Q-LES-Q-SF	Quality of life	Self	10	Baseline	✓	✓
				Session 10	✓	✓
				End of study	✓	✓
BADS	Measure activation and avoidance behaviours	Self	5–10	Baseline	✓	✓
				Weekly	✓	
				End of study	✓	✓
LMS	Measure motivation for engaging in leisure activities	Self and clinician (observational)	15–30	Baseline	✓	✓
				Session 10	✓	
				End of study	✓	✓
EQ-5D-5 L	Health-related quality of life to generate health utility index for calculation of quality-adjusted life years for economic evaluation	Self	5	Baseline	✓	✓
				End of study	✓	✓

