### Outcomes

#### Pilot study outcomes

*Primary*:Assess the feasibility of the study process in terms of recruitment, retention, number of sessions completed, average group size and data completion.To assess resources needed including the use of interview rooms, group room, mobile computers to upload activity-tracking data, communication with participants’ clinicians and time investment in the program by the study clinicians.The qualitative component of the pilot study is to assess the need to modify the protocol for the main trial based on the participants’ feedback thus aiming to provide a patient-centred treatment program.

*Secondary*:Assess the change in mood using the Beck Depression Inventory between and within the intervention and control groups.Explore the change in quality of life scores between and within the intervention and control groups.

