### Sample size

For the feasibility and pilot trial, we will recruit 10 participants in each arm. This number is based on the recommended group therapy size of 6–12 per group session. The pilot data will help to modify the sample size calculation for the main trial.

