### Allocation and randomization

We will employ a parallel group design to test the feasibility of behavioural activation study in depression. Eligible and consenting patients will be randomly allocated to the intervention or control arms using a 1:1 allocation ratio. Allocations will be randomly assigned using a block randomization system of block sizes of 2, 4 and 6.

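### The between-arm comparison is an unadjusted t test of end-of-trial scores, although the objective is change and baseline scores are collected in both arms

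*Protocol article*

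**What the plan says.** All references are to the Protocol article.

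- **Objective.** The secondary outcomes under Pilot study outcomes (repeated under Pilot study secondary objectives) are "Assess the change in mood using the Beck Depression Inventory between and within the intervention and control groups" and "Explore the change in quality of life scores between and within the intervention and control groups".
- **Between-arm method.** Statistical analyses plans the mean difference with 95% CI "of the BDI-II and quality of life scores between intervention and comparator groups at the end of the trial", by t test. No baseline term or change score is mentioned.
- **Within-arm method.** Repeated measures enter only within each arm: "and within groups for repeated measures using analysis of variance (ANOVA". Table 2 refers to comparisons between and within groups and adds no adjustment.
- **Baseline data.** Table 1 schedules the BDI-II (purpose: "Monitor depressive symptoms"), SF-12, WSAS and Q-LES-Q-SF at baseline and at end of study in both arms.
- **Size and allocation.** Under Sample size, "we will recruit 10 participants in each arm". Under Allocation and randomization, "Allocations will be randomly assigned using a block randomization system of block sizes of 2, 4 and 6". No stratification by severity is stated.
- **Status.** Statistical analyses calls these comparisons exploratory and says the sample size does not permit definitive ones.

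**The concern.** The objective asks how the arms differ in change, but the stated between-arm analysis uses only the final score. The one analysis that uses earlier scores is done separately within each arm and gives no between-arm estimate. A reader who wants between-arm change may then compare two within-arm changes informally, which is not a valid comparison of the arms.

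With 20 participants in total, the arms can easily differ at the start by chance. An unadjusted end-score comparison carries part of that difference into the estimate, and the information that would remove it has already been collected. At stake are the closeness of the pilot's between-arm clinical estimate to the treatment difference and the width of its interval. The protocol itself fixes the time point and the test, so the point concerns a stated choice and not a detail left to a later analysis plan.

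**Working it through.** **Inputs.** n = 10 per arm (Sample size). The 80% completion criterion (Statistical analyses) gives 0.8 × 10 = 8 per arm with final data. The protocol states no SD, no baseline-to-final correlation and no power figure, so there is nothing of its own to reproduce. Results are in SD units, with equal SDs and r assumed over 0.2 to 0.7.

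**Step 1: chance baseline imbalance.** SE of the baseline difference = √(2/n).

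- n = 10: √(2/10) = 0.447 SD. 95% range ±1.96 × 0.447 = ±0.88 SD. P(|difference| > 0.5 SD) = 2[1 − Φ(0.5/0.447)] = 0.264.
- n = 8: √(2/8) = 0.500 SD. P(|difference| > 0.5 SD) = 2[1 − Φ(1)] = 0.317.

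**Step 2: carry-over of a baseline imbalance d.** The expected shift is r × d for the end-score t test, (r − 1) × d for a change-score t test, and 0 for ANCOVA. With d = 0.5 SD:

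| r | End score | Change score | ANCOVA |
|---|---|---|---|
| 0.2 | 0.10 | −0.40 | 0 |
| 0.3 | 0.15 | −0.35 | 0 |
| 0.5 | 0.25 | −0.25 | 0 |
| 0.7 | 0.35 | −0.15 | 0 |

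A simulation of 40,000 trials with 10 per arm and no treatment effect agrees. Among trials with a baseline difference between 0.4 and 0.6 SD, the mean end-score difference was 0.135, 0.251 and 0.347 SD at r = 0.3, 0.5 and 0.7. ANCOVA gave −0.012, 0.007 and 0.004 SD.

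**Step 3: precision with 10 per arm.**

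- End-score t test: SE = √(2/n) = 0.447. Half-width of the 95% CI = t(18) × 0.447 = 2.101 × 0.447 = 0.94 SD.
- Change score: SE = √(2/n) × √(2(1 − r)).
- ANCOVA: SE = √(2/n) × √(1 − r²) × √(1 + 1/(2n − 4)). Half-width = t(17) × SE, with t(17) = 2.110.

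| r | Change-score SE | ANCOVA SE | ANCOVA half-width | t test half-width |
|---|---|---|---|---|
| 0.2 | 0.566 | 0.452 | 0.95 | 0.94 |
| 0.3 | 0.529 | 0.440 | 0.93 | 0.94 |
| 0.5 | 0.447 | 0.399 | 0.84 | 0.94 |
| 0.7 | 0.346 | 0.329 | 0.69 | 0.94 |

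**Step 4: the same with 8 per arm.** The t test half-width is 1.07 SD. ANCOVA gives 1.10, 1.07, 0.97 and 0.80 SD at r = 0.2, 0.3, 0.5 and 0.7, so at this size the precision gain appears only above r of about 0.3.

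**Step 5: choice of adjustment.** A t test on change scores would match the wording of the objective. It over-corrects for imbalance at every r below 1, and below r = 0.5 it is less precise than the end-score test. ANCOVA avoids both problems.

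**The case against.** The strongest reply is that the planned test is valid. Over repeated randomisation the end-score difference and the difference in change target the same treatment effect. The 0.94 SD half-width already allows for chance imbalance, and the comparison is secondary, exploratory and not a test of effectiveness. All of this stands. It means the issue is conditional bias and efficiency, not an invalid analysis, and the mismatch with the word change is mild. It does not remove the case for using baseline data already in hand.

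Some stronger readings are tempting but unsupported:

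- **Imbalance passes in full, or the result mainly reflects who started sicker.** Imbalance is multiplied by r. Baseline explains r² of the chance variance in the end-score difference, which is 4% at r = 0.2, 25% at 0.5 and 49% at 0.7. This is under half throughout the assumed range.
- **Open entry makes the baseline spread wide and so imbalance likely.** In SD units the imbalance is 0.447 whatever the spread. Study setting also suggests that these patients sit towards the severe end.
- **The BDI-II will be compared between arms in categories.** Data collection methods says "The BDI-II score is analyzed using four categories of depressive symptom severity", but the sentence belongs to a description of the instrument. Neither Statistical analyses nor Table 2 plans a categorical comparison.
- **The effect estimate will be carried into the main trial.** Sample size says only that pilot data will help revise that calculation, and the SD of the scores is available under either method.

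**Conclusion.** The point holds as a low-to-moderate one: the authors should fix it, but the pilot does not depend on it. The stated between-arm analysis ignores baseline scores that bear directly on the stated objective. There is a 26% chance of a baseline difference above 0.5 SD with 10 per arm, or 32% with 8. At exactly 0.5 SD the estimate shifts by 0.10 to 0.35 SD across the assumed r. The gain in precision is negligible at r = 0.3 and material at 0.5 to 0.7. At r = 0.2 there is none, and removal of the conditional bias is then the only benefit.

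These sizes rest on equal SDs and an assumed r. The three feasibility criteria (20% enrolment, 80% final-visit data, 80% of weekly scales) do not depend on this comparison.

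**What to change.** In Statistical analyses, replace the between-arm t test with ANCOVA of the final continuous score on arm and the baseline score of the same scale. Do this for the BDI-II and for each of SF-12, WSAS and Q-LES-Q-SF. Report the adjusted mean difference with its 95% CI and label it exploratory. The within-arm description can stay. A clause saying that the four BDI-II severity categories are descriptive would prevent misreading.

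The cost is one sentence of wording and one degree of freedom, with no new data. The interval becomes marginally wider if r is about 0.2 or less (0.95 against 0.94 SD with 10 per arm). ANCOVA also yields the residual SD and an estimate of the baseline-to-final relation, both useful in planning a main trial, though imprecise at this size.

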### Qualitative data analysis

The focus group sessions will be recorded using three devices in efforts to ensure that data are properly captured and to avoid any recording malfunction. Conversations will be transcribed in real-time by co-facilitators, and audio recordings will be used to verify these transcriptions. Facilitators will take extensive field notes, track participant responses, and ensured data are adequately collected from research participants.

We will use the analytical techniques of grounded theory, including line-by-line coding, thematic coding and constant comparative analysis [35, 41, 42]. These techniques require the analyst to look at small pieces of the data and then group and re-group the data into different categories. Additional data requires the entire dataset to be re-read and re-analyzed, to ensure the categories are still comprehensive and relevant. Data analysis will begin as soon as the first data are collected, and emerging findings will inform future data collection [35]. Three members of the research team individually reviewed the transcripts of the focus group to inductively identify themes before further analysis of the data. After further coding of the identified themes, they created an inclusive master list of themes. Dissenting opinions will be discussed and resolved. NVivo 9 software will be used to facilitate data management and analysis.

### Data monitoring

The main concern for this type of study is the presence of suicidal risk in the intervention and control groups. Suicide risk is increased in depressive disorders, and a specific question in the depression symptoms score using BDI-II is dedicated to suicidal ideas. Therefore, monitoring this specific question is important during the study. For this reason, the BDI-II questionnaires will be completed at the clinic and the answers checked by the clinician while the participants are in the program. If the suicide question is checked positive, the patient will be asked to stay in the clinic, and the patient psychiatric care provider will be informed. This is a common practice for clinical and research processes taken place at the mood disorders clinic. The use of BDI-II is also a common practice, and all clinicians are familiar with scoring and checking the suicide question.

This study does not require a data and safety monitoring board due to the reasons described above in a social/behavioural research type of study.

### Harms

This study is a minimal risk non-pharmaceutical study; however, there may be risks involved including anxiety or fatigue when completing the study questionnaires, interviews and attending groups. In addition, participants allocated to the control group may feel disappointed that they did not receive the new intervention. The study investigators interviewing participants and administering intervention/control conditions are experienced clinicians delivering psychiatric care at the clinic; in addition, all participants will also continue to have usual care. The study clinicians will be in close contact with participants’ clinical teams. If participants are seen in distress, fatigue or anxious situations, the clinician will attend to the participant needs and remove them from the group/study if necessary.

### Auditing

The study team will meet weekly to discuss the study progress and review the weekly report of study recruitment, data quality and monitoring of attendance and any issues raised by the participants or the clinicians.

